### Data processing

#### Procedures

This study complies with the Declaration of Helsinki and will be conducted in accordance with the principles of Good Clinical Practice (GCP). Standardized processing files for obtaining informed consent, measurement procedures, reporting (serious) adverse events (AEs), and recording patient and measurement data parameters in electronic case report file (eCRF) are available. Investigators obtaining patient informed consent, conducting UHF MRI scans, and recording eCRF data will have received specific training beforehand.

#### Data management

Patients’ demographic and clinical data are recorded in an eCRF at a secure encrypted database (Castor Electronic Data Capture), which enables an audit trail and is GCP certified. Reconstructed MRI data of all patients will be stored in the Radiology Research Server of ACE MUMC + , and outcome is recorded anonymized in the eCRF. After verification of recorded data to source data by one of the executive investigators, recorded data in the eCRF by Castor EDC will be exported to an SPSS file for further statistical analysis.

Patients will be assigned a numeric sequential study number to identify all clinical data, documented in a separate screening database held on a secure computer at the including study site. Source data, code encrypting document, and coded data in the study database are locked and only accessible to the principal and executive researchers and monitors. In each patient file, we will note coded information under which results are traceable, ensuring that the epilepsy surgery workgroup can have access to all possible useful information. Additionally, the “Inspectie Gezondheidszorg en Jeugd” (healthcare and youth inspection) will be provided with the possibility to review research data whenever this is required. On completion of the study, the study database will be locked and data are securely archived for 15 years in accordance with local policy.

### Safety

The clinical trial sponsor (MUMC +) and principal investigators ([name] and [name]) have overall responsibility for the execution of this study including safety. Individual investigators will be responsible for reporting AEs and serious AEs (SAEs) to the principal investigators. SAEs are defined as AEs resulting in death, life-threatening events, prolonged hospital stays, or significant disability. Up till now, there are no reported (S)AEs associated with the clinical use of UHF MRI in literature. UHF MRI is, with regard to safety, highly comparable to standard MRI scanning at 3 T for clinical health care when safety precautions are taken into account [36, 37]. The MRI safety relevant inclusion/exclusion criteria for 7 T and 9.4 T are set by the local Safety Review Board (SRB), which acts as an expert advisory panel on behalf of the local Medical Ethical Committee/Institutional Review Board (IRB). The MRI-questionnaire determines whether a patient is eligible and safe to undergo the scan.

Claustrophobia can be a possible concern of UHF MRI, due to a longer magnet bore. However, this is accounted for by excluding patients with known claustrophobia. Also, all subjects already underwent a clinical 3 T MRI scan; any occurrence of adverse events during this scan would lead to exclusion of the subject. One important frequently reported side-effect at UHF is vertigo when moving in/out the bore, in some cases resulting in nausea or small involuntary eye motion, i.e., nystagmus [38]. However, this poses no health threat to patients [36]. In case patients experience uncontrollable nausea, scanning will be stopped immediately. All events or complaints from signing informed consent until 1 day after completion of the UHF MRI scan will be considered an adverse event, and are reviewed by the principal investigator to decide if there is a causal link and, when applicable, appropriate action will be undertaken. Follow-up in patients will continue until minimally 1 year after epilepsy surgery. Due to the nature of the investigated pathology (epilepsy), seizures and subsequent sequelae between completion of the UHF MRI scan and 1-year follow-up will not be considered an adverse event related to study procedures. SAEs will be reported through the web portal to ToetsingOnline to the IRB (METC azM/UM). Liability and subject study-related insurance are provided.

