### Inclusion and exclusion criteria

For the present study, we include pediatric patients (children, aged 12–17 years) and adults (aged 18 and above), with drug-resistant focal epilepsy (ongoing seizures despite at least two adequate and well-tolerated anti-epileptic drugs trials [29]), who are under evaluation for resective epilepsy surgery. All patients have had a clinical 3 T MRI without an identified explanatory epileptogenic lesion. Exclusion criteria are intellectual disability (IQ < 70), incapacity to sign informed consent, pregnancy, and criteria specific for UHF MRI (see Table 1).

**Table 1 Tab1:** Overview of inclusion and exclusion criteria

Inclusion criteria
Age ≥ 12 years
Drug-resistant focal epilepsy
Work-up for epilepsy surgery
Clear suspicion on the focal onset of the epilepsy
Absent explanatory abnormalities on conventional 3 T MRI
Informed consent signed
Exclusion criteria
Incapacitated to sign informed consent
Patients and/or legal representative have an intellectual disability (IQ < 70)
Pregnancy
MRI-exclusion criteria:
Claustrophobia
Pacemaker, neurostimulor, insulin pump or other pump
Aneurysm clips in cerebro not safe at 7 or 9.4 T MRI
Metal particles in the head (incl. eye)
Hearing prostheses (not all types)
Tattoos above the diaphragm
Other body implants not proven safe at 7 or 9.4 T MRI
Relative contra-indications depending on place and kind
Artificial heart valves
Joint prostheses
Obesity making MRI-scanning impossible due to size

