### Sample size

The primary study outcome is the lesion detection rate of UHF MRI. This outcome will be estimated without formal null-hypothesis testing. We previously conducted a study in which we included 19 adult patients where MEG directed to an epileptogenic lesion [35]. All patients were 3 T negative; on 7 T, six patients showed possible epileptogenic lesions. However, as there is no similar research based on other examination modalities (SPECT, PET, etc.) available for UHF MRI imaging, no data to perform a sample size calculation is available [23, 24]. Therefore, we take a pragmatic approach to the determination of sample size. Rules of thumb for linear regression analysis state that at least 10 observations are needed for each variable that is entered in the regression model. In addition to univariate analysis, we aim to perform multivariable analysis in which we will correct for up to five potential confounding variables. Hence, we will need to include at least 60 patients for this study. With a sample of this size, the margin of error (i.e., half-width of the 95% confidence interval) of the detection rate will likely be below 0.20.

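### For a seizure on the first day after a UHF scan, the Safety section both requires a causality review and rules out a causal link in advance

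*Protocol article*

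**What the plan says.** All the relevant rules stand in the Safety section of the protocol article.

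- **The AE window.** "All events or complaints from signing informed consent until 1 day after completion of the UHF MRI scan will be considered an adverse event". It makes no exception for seizures. These events "are reviewed by the principal investigator to decide if there is a causal link".
- **The seizure sentence.** Because of the disease under study, "seizures and subsequent sequelae between completion of the UHF MRI scan and 1-year follow-up will not be considered an adverse event". The sentence does not end there: it closes with a qualifier, that the adverse event meant is one related to study procedures.
- **Serious events.** "SAEs will be reported through the web portal to ToetsingOnline to the IRB". This route is not restricted to events judged related.

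Two other places matter. The inclusion criteria define the population by "ongoing seizures despite at least two adequate and well-tolerated anti-epileptic drugs trials", so seizures after a scan are to be expected. The timeline in the section on recruitment capacity, consent and timeline gives every patient a 7 T scan, and gives the first ten 7 T-negative patients a 9.4 T scan on another day.

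**The concern.** The AE window closes 1 day after the scan, while the seizure sentence opens at scan completion. The two therefore overlap for the first post-scan day. For a patient with one scan, that day is the only part of the AE window that follows exposure, so it is where a delayed effect of scanning could be recorded.

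For a seizure in that day, the first rule calls for a case-by-case decision on causality, and the second settles the answer beforehand for the whole class of event. A site can follow either sentence and be within the protocol. Recruitment runs at Dutch and German sites, and the monitors who review AE reporting have no single rule to check against. What is at stake is consistent recording and an open causality judgement in a short safety window. The detection-rate and seizure-outcome estimates are not affected.

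**Working it through.** The plan gives no figure to reproduce on this point. The check compares the two rules and then illustrates how much patient time the overlap covers.

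**Step 1. The rules by time of the seizure**

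| Time of seizure | AE-window sentence | Seizure sentence | Result |
|---|---|---|---|
| Consent to scan completion | AE, causality reviewed | Does not apply | Clear |
| Scan completion to 1 day after | AE, causality reviewed | Declared not study-related | Conflict |
| More than 1 day after, up to 1-year follow-up | Outside the window | Declared not study-related | Clear |

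Only the middle row conflicts. A seizure before or during the scan goes to causality review, while one an hour after the scan is ruled unrelated without review, if the seizure sentence prevails.

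**Step 2. Two readings of the seizure sentence**

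- *Attribution only.* The closing words on study procedures limit the sentence to relatedness. The seizure stays an AE, but its causality is fixed in advance, against the planned review.
- *AE status.* The sentence takes the seizure out of the AE category. It then contradicts the AE-window sentence on status as well as on causality.

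The conflict over causality exists on both readings. The conflict over AE status exists only on the second.

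**Step 3. Which scan starts and ends the windows**

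Both sentences refer to completion of the scan in the singular, but ten patients have two scans on different days. If the AE window runs to 1 day after the last scan and the exemption starts at the first, the conflict in those ten patients covers the whole interval between scans plus 1 day. If each scan has its own window, the overlap is 1 day per scan.

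**Step 4. Illustrative size**

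Inputs:

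- 60 patients, from the Sample size section ("we will need to include at least 60 patients for this study").
- 10 additional 9.4 T scans, from the timeline.
- Seizure frequency: not given in the article. The rates below are assumptions.

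Scan-days in the overlap = 60 + 10 = 70.

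Expected seizures = 70 × daily rate. With a Poisson count, P(at least one) = 1 − exp(−expected).

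| Assumed mean rate | Daily rate | Expected seizures in overlap | P(at least one) |
|---|---|---|---|
| 1 per year | 1/365.25 | 70/365.25 = 0.19 | 1 − exp(−0.19) = 17% |
| 1 per month | 12/365.25 | 70 × 12/365.25 = 2.3 | 1 − exp(−2.3) = 90% |
| 1 per week | 1/7 | 70/7 = 10 | 1 − exp(−10) > 99.9% |

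Unless seizures are rare in this cohort, the overlap day will probably contain some. These are seizures of any kind. The figures say nothing about how many would be serious.

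**The case against.** The best defence is that the seizure sentence, read to its end, only denies attribution. On that reading a post-scan seizure remains an AE, and a reader who infers that it loses AE status has adopted one of two readings. That stands. It narrows the conflict to causality but does not remove it, because an advance ruling and a case-by-case review cannot both govern the same event.

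A reader might also infer that serious seizures could go unreported. The article does not support this. Serious AEs go to the IRB whether or not they are judged related, so on the attribution reading a fatal, life-threatening or disabling seizure on that day is still reportable.

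A further inference concerns the definition of a serious event: "SAEs are defined as AEs resulting in death, life-threatening events, prolonged hospital stays, or significant disability". It names no first admission. But this is a one-clause summary in a journal article, and the Procedures section says that standardized files for reporting (serious) AEs exist. The fuller definition may well stand there, so its brevity here is not a finding.

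Finally, the study has no safety outcome and reports no AE rate, so no stated estimate would change. That is correct and limits the weight of the point. Condensation is a weaker defence for the overlap itself, since both rules are printed in full and neither yields to the other.

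**Conclusion.** The point holds as an internal contradiction over causality, confined to the first day after each UHF scan: about 70 scan-days if each scan has its own window, and more if the windows of the ten two-scan patients run from the first scan to the last. That seizures also lose AE status is a possible reading but not an established one.

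The number of seizures affected cannot be derived from the article. The range in the working, from 0.19 to 10 expected seizures, rests on assumed rates and on seizures occurring independently at a constant rate; clustering within patients would lower the probability of at least one. The article gives no rate of serious events, so it does not support describing a post-scan seizure as the most foreseeable serious one.

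This is a modest point with no bearing on the primary outcomes. It is worth correcting because it prejudges causality on the day after exposure, and because the correction is nearly free.

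**What to change.** Reconcile the two sentences in the Safety section so that the seizure exemption begins only when the 1-day window has closed. State that the window applies after each UHF scan, including the separate 9.4 T scan. Seizures inside it are recorded as AEs and go through the principal investigator's causality review already planned. They may be tabulated on their own line, so that expected background seizures are not mixed with other events.

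The cost is about one sentence of protocol text and slightly more AE recording. No outcome, sample size or analysis changes.

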### Statistical analysis

Baseline characteristics of the cohort will be described in detail as mean and standard deviation or median and interquartile range for continuous variables (depending on their normality of distribution) and as count and percentage for categorical variables. Missing values are unlikely to occur, but in case of incomplete MRI data, we will use stochastic regression imputation to facilitate the inclusion of all study participants in the analyses.

UHF MRI data, such as characteristics of and, if applicable, localization of abnormalities, will be summarized using descriptive statistics. Primary outcomes diagnostic and therapeutic gain will be expressed as point estimates with 95% confidence intervals. Explorative analysis is used for quantitative MRI measurements (diffusion, fMRI, ASL). Radiological assessment will be done independently, in case of different results consensus will be sought. Intra-observer and inter-observer agreement in assessing MRI images will be quantified using Cohen’s kappa for categorical MRI parameters, and intra-class correlation coefficient (ICC) for continuous MRI parameters. Associations between qualitative findings and histopathological abnormalities will be computed using Spearman rank correlation, point bi-serial correlation, or Fisher’s Exact test, depending on the distribution of the findings.

We will assess the association between demographic, clinical parameters, and outcome measures by using univariable and multivariable regression analysis. A *p*-value of < 0.05 will be considered statistically significant. Statistical analysis will be performed using IBM SPSS software version 25 or higher.

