### Outcome parameters

The primary outcome parameter of this study is the number of patients with detected “epileptogenic” structural and functional brain abnormalities on 7 T and 9.4 T UHF neuroimaging, the so-called “diagnostic gain” in patients with 3 T MRI-negative drug-resistant focal epilepsy. The second primary outcome parameter is postoperative seizure outcome (ILAE/Engel class at 12 months) in operated UHF MRI-positive versus MRI-negative patients “i.e., therapeutic gain.”

As secondary outcome parameters, detection rate of UHF resting-state fMRI for cortical abnormalities in spontaneous blood oxygenation level-dependent (BOLD) signal fluctuations as a marker of an epileptogenic lesion, concordance of UHF MRI imaging with histopathological diagnosis of surgical specimen, intra- and inter-observer agreement for UHF MRI evaluation, and association between ROIs in the non- or semi-invasive work-up modalities and UHF MRI data will be assessed.

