### Challenges

Sample size calculation for a study assessing diagnostic gain and improvement of postoperative seizure outcome is not trivial as there is no comparable research based on other modalities (SPECT, PET, etc.). Thus, no power calculation based on prior studies can be performed. Therefore, we took a pragmatic approach with sample size calculation based on observations needed for each variable entered in a regression model. Final study power has to be established.

The main technical challenges for UHF MRI acquisition are inhomogeneities in the main magnetic field (*B*_0_) and radiofrequency transmit field (*B*_1_) and their stronger interaction with any implants. The current proposed scan protocol might lead to increased sensitivity to motion artifacts due to longer scanning times in the chosen highest resolution protocols, as the patient has to lie still for a longer period of time. Our total scan time of ± 70 min is slightly above acquisition times of other 7 T studies, where acquisition time was not an issue [23, 31, 35, 47]. Additionally, clinical 3 T MRI is performed at an earlier stage than UHF MRI in the epilepsy surgery workup. The results of additional examinations possibly lead to novel insights on the ROI, influencing reviewing of UHF MRI scans. A potential bias may occur because not all patients receive all other non-invasive examinations, but at the clinician’s discretion. Furthermore, inexperience in clinical reading/interpretation of 7 T and 9.4 T images can be an issue, as reviewers might experience a reviewing learning curve. Also, UHF might produce artifacts or geometric disturbances not seen on conventional MRI, potentially resulting in detection of non-relevant lesions (false positives). To address this issue, several UHF pilot scans will be performed to gain experience at reviewing UHF MRI. This includes patients with positive 3 T MRI for a small lesion, along with non-epileptic volunteers.

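### Single stochastic imputation of incomplete MRI data is not barred from the primary lesion reading, so a simulated reading could be analysed as observed

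*Protocol article*

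**What the plan says.** The Statistical analysis section opens its missing-data rule with "Missing values are unlikely to occur" and continues that "in case of incomplete MRI data, we will use stochastic regression imputation to facilitate the inclusion of all study participants in the analyses". It mentions neither multiple imputation nor pooling of variances, and it does not limit the rule to particular MRI variables.

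The section on outcomes defines the first primary outcome this way: "The primary outcome parameter of this study is the number of patients with detected “epileptogenic” structural and functional brain abnormalities on 7 T and 9.4". The quotation stops at the second of the two field strengths; the patients concerned are those negative at 3 T. The second primary outcome compares seizure outcome at 12 months between operated patients who are positive and negative on UHF MRI. Both therefore depend on an MRI reading. On reporting, "Primary outcomes diagnostic and therapeutic gain will be expressed as point estimates with 95% confidence intervals". The Sample size section says of the detection rate that "This outcome will be estimated without formal null-hypothesis testing".

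Two places name ways in which a scan could be cut short or degraded. Safety: "In case patients experience uncontrollable nausea, scanning will be stopped immediately". Challenges: the proposed scan protocol "might lead to increased sensitivity to motion artifacts due to longer scanning times", with a total scan time of about 70 minutes.

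**The concern.** Diagnostic gain is a count of lesions that readers detected. If a scan is aborted or cannot be read, nobody detected anything, and that failure is itself a result of the technique. A lesion status predicted from covariates plus a random draw is not a detection.

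The second primary outcome is exposed in the same way. The article's hypothesis is that a detected lesion guides the resection. An imputed positive has no location and could have guided nothing, so that patient's exposure would be misclassified. The operated patients are a subset of the cohort, so each such patient weighs more there.

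The second problem is one of variance. With one imputed data set, the usual interval treats all 60 readings as observed. It ignores both the smaller number of real readings and the noise added by the draw.

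**Working it through.** **The plan's own figures first.** "Hence, we will need to include at least 60 patients for this study" follows from 10 observations for each of 5 confounders plus 1 main variable: 10 × 6 = 60. The earlier study cited under Sample size found possible lesions in 6 of 19 patients, so p = 6/19 = 0.316. The Wald half-width at n = 60 is 1.96 × √(0.316 × 0.684 / 60) = 1.96 × 0.0600 = 0.118; at p = 0.50 it is 0.127. Both agree with the stated margin of below 0.20.

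**Inputs for the check.** n = 60 and p = 6/19, from the article. The number m of scans with no lesion reading is an assumption, because the article gives none; the table uses m = 0, 3, 6 and 12 (0%, 5%, 10%, 20%). Readings are taken as missing completely at random.

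**Formula.** The completed-data estimate is (observed positives + imputed positives)/n. Given the observed data its mean is the observed rate, so its variance is approximately p(1−p) × [1/(n−m) + m/n²]. The completed-data interval uses p(1−p)/n. The ratio of true to reported variance is

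R = n × [1/(n−m) + m/n²].

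The standard error is understated by 1 − 1/√R. Approximate coverage of a nominal 95% Wald-type interval is 2Φ(1.96/√R) − 1.

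- m = 3: R = 60/57 + 3/60 = 1.053 + 0.050 = 1.103; √R = 1.050
- m = 6: R = 60/54 + 6/60 = 1.111 + 0.100 = 1.211; √R = 1.101
- m = 12: R = 60/48 + 12/60 = 1.250 + 0.200 = 1.450; √R = 1.204

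| Unreadable (assumed) | SE understated | Approx. Wald-type coverage | Half-width reported | Half-width needed | Half-width, readable scans only | Wilson coverage after imputation (simulated) |
|---|---|---|---|---|---|---|
| 0 | 0% | 95.0% | 0.1176 | 0.1176 | 0.1176 | 96.4% |
| 3 | 5% | 93.8% | 0.1176 | 0.1235 | 0.1207 | 95.4% |
| 6 | 9% | 92.5% | 0.1176 | 0.1294 | 0.1240 | 94.4% |
| 12 | 17% | 89.6% | 0.1176 | 0.1416 | 0.1315 | 91.8% |

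The simulation used 400,000 runs at p = 6/19. In it the standard deviation of the imputed estimate rose from 0.060 to 0.063, 0.066 and 0.072, as the formula predicts. With a moderately predictive covariate in the imputation model (assumed rates of about 0.15 and 0.48 in two equal groups), the ratio of true to reported standard error was still 1.05, 1.09 and 1.17.

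The imputed estimate needs a wider interval than an analysis of readable scans alone. The single draw thus adds noise, and the reported interval then hides it.

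**Point estimate.** Counting unreadable scans as not detected gives 0.316 × (60−m)/60 = 0.300, 0.284 and 0.253. That is 1.6, 3.2 and 6.3 points below the imputed estimate, which stays centred on 0.316. Counting them all as detected gives 0.350, 0.384 and 0.453.

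**The case against.** The strongest reply is that the sentence speaks of incomplete MRI data, not of failed scans, and never says that lesion status will be imputed. The proposed protocol has eight numbered sequences. An examination without ASL or DTI may still be fully readable, and its lesion status is then observed. MRI data also include continuous measures such as lesion volume and the exploratory diffusion, fMRI and ASL values, for which regression imputation is a natural idea. This stands as a limit. A reader might infer that the plan sets out to invent lesions for failed scans, and the text does not say that. It does say that imputation serves to bring all participants into the analyses, and it leaves the lesion reading within the rule.

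A reader might also infer that calling missing values unlikely contradicts the remarks on nausea and motion. It does not. The Challenges section adds that acquisition time was no problem in other 7 T studies with slightly shorter scans. The Safety section excludes patients with known claustrophobia or with adverse events at 3 T. A possible failure can be named and still be thought unlikely.

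A third tempting reading is that coverage always falls below 95%. With Wilson intervals it stays above 95% at 3 of 60 missing, and the article does not name an interval type. Discreteness alone matters as much at this size: Wilson intervals on readable scans only had simulated coverage of 93.8%, 94.5% and 95.8% at 3, 6 and 12 missing.

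Nor are the gaps of 3.2 and 6.3 points a demonstrated bias. They separate two legitimate questions: what UHF MRI yields over everyone scanned, and what it yields when the scan can be read. Finally, nothing suggests that 9.4 T results would be imputed for patients never chosen for that scan; the article limits 9.4 T to the first ten patients negative at 7 T.

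**Conclusion.** The point holds in a limited form. The article fixes a single-imputation rule for MRI data and does not exempt a primary outcome that is an MRI reading. For any patient without a reading, following the rule would enter a simulated status in both primary outcomes and treat it as observed. This objection of principle applies from the first such patient and does not depend on the missing fraction.

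The effect on the intervals does depend on it. It is minor at 5% missing or less and becomes material from about 10%, under the assumptions of p = 6/19, data missing completely at random and Wald-type intervals. Even at 20% the half-width needed, 0.142, is below the stated 0.20. The sample size of 60 is untouched, and no hypothesis test of the detection rate is affected. If every incomplete examination turns out to be readable, the primary detection rate is not affected at all. The rule should be fixed, but it is not a flaw that must be cured before the study can be relied on.

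**What to change.** Replace the imputation sentence with a short rule in two parts.

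1. **Lesion status is not imputed.** Report the number of non-diagnostic scans. Give the primary detection rate over all scanned patients, with non-diagnostic scans counted as not detected, and show the rate among readable scans as a sensitivity analysis. State that an examination with missing sequences that can still be read keeps its observed reading. In the comparison of operated patients, count no one as UHF-positive without an actual reading.
2. **Missing covariates or quantitative MRI measures in the regressions** are handled by multiple imputation with pooled variances, which is available in SPSS, the software already named.

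The rule should be settled before the number of failed scans and their likely influence are known. The cost is a few sentences and no extra patients or scans. The downside is a slightly lower detection rate if scans fail, because the rate then reflects feasibility as well as visibility of lesions, and slightly wider intervals.

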
Results of the UHF MRI scans will be presented and discussed in a monthly multidisciplinary epilepsy surgery conference. We will evaluate the association between the presence and absence of an abnormal finding, with information of other non-invasive examinations. Additionally, we will assess the potential improvement in detection rate after adding prior knowledge of the ROI to the results of reviewing, by comparing the first with the second run, along with intra-observer and inter-observer variability.

After obtaining UHF MRI results, patients can undergo either (1) resective epilepsy surgery, (2) implantation of intracerebral depth electrodes for intracranial EEG recordings (S-EEG), (3) S-EEG guided radiofrequency thermo coagulation (RFTC), or (4) proceed to palliative treatment options (e.g., vagus nerve stimulation). Surgical resection is the first choice due to its efficacy and will be performed when possible, with regard to lesion location, extent, and expected lesion etiology. Depth electrode implantation will be used when additional information on the possible epileptogenic zone is required. S-EEG RFTC will be performed when resective surgery is not recommended, for example, in case of deep-seated periventricular heterotopias. Palliative treatment options are explored when other curative treatments are excluded. Samples of surgically treated patients will be examined by routine histopathological analysis and classified according to ILAE guidelines [20]. In case of resective epilepsy surgery, UHF MRI–based diagnosis will be compared to histopathological diagnosis. Postoperative seizure outcome following ILAE and Engel classification [34] will be assessed by the treating neurologist as standard care minimally 1 year after surgery.

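### The plan makes concordance of UHF MRI with histopathology a secondary outcome, but the only MRI-versus-histopathology analysis it names measures association, not agreement

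*Protocol article*

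**What the plan says.** Three places in the protocol article bear on this point.

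- **Outcome parameters** lists among the secondary outcomes "concordance of UHF MRI imaging with histopathological diagnosis of surgical specimen".
- **Intervention and evaluation protocol** makes this a comparison of diagnosis with diagnosis in resected patients: "UHF MRI–based diagnosis will be compared to histopathological diagnosis". Specimens are "examined by routine histopathological analysis and classified according to ILAE guidelines". No ordering of the classes is given.
- **Statistical analysis** has one sentence relating MRI to histopathology: "Associations between qualitative findings and histopathological abnormalities will be computed using Spearman rank correlation, point bi-serial correlation". It then offers Fisher's test as a third option and lets the choice depend on how the findings are distributed. The sentence just before it deals with agreement, but only between readings: "Intra-observer and inter-observer agreement in assessing MRI images will be quantified using Cohen’s kappa for categorical MRI parameters", with the intraclass correlation for continuous parameters. The section also sets a general threshold: a p-"value of < 0.05 will be considered statistically significant".

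No agreement measure is named for MRI against histopathology.

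**The concern.** Concordance asks whether the UHF diagnosis is the same as the pathologist's. Association asks only whether the two classifications are related. A strong association is compatible with any level of agreement, including none. The plan uses agreement statistics between readers but names only association statistics against the tissue diagnosis, so the mismatch shows within one paragraph.

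The three methods fall short for different reasons:

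- Fisher's exact test is valid for nominal classes, but it tests independence and returns no measure of agreement.
- Spearman's rho needs ordered categories. With three or more unordered classes, its value depends on the code numbers given to them.
- Point-biserial correlation needs one binary and one continuous variable. A comparison of two diagnoses has no continuous variable.

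The choice among them is also tied to the distribution of the findings. It should follow the measurement scale, which is known before any data are seen.

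The Challenges section warns that UHF artefacts may produce false-positive lesions. The comparison with histopathology bears directly on that risk. A p-value or a coding-dependent coefficient would not tell the reader how often the UHF diagnosis was right.

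**Working it through.** The plan states no figure for this outcome, so there is nothing to reproduce. The number of patients who will be operated on is not given either; only the total of 60 is (Sample size). All tables below are constructed illustrations. Rows are the UHF class and columns the histopathology class.

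**1. Fisher's exact test, two classes, 20 specimens**

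All margins are 10 in both tables. The two-sided p is 2 × [C(10,9)·C(10,1) + 1] / C(20,10) = 2 × 101 / 184,756 = 0.00109. Kappa is (observed − expected agreement) / (1 − expected), with expected agreement 0.5.

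| Table | Agreement (exact 95% CI) | Fisher p | Kappa | Spearman rho |
|---|---|---|---|---|
| [[9,1],[1,9]] | 18/20 = 90% (68% to 99%) | 0.00109 | (0.9 − 0.5)/0.5 = +0.80 | +0.80 |
| [[1,9],[9,1]] | 2/20 = 10% (1% to 32%) | 0.00109 | (0.1 − 0.5)/0.5 = −0.80 | −0.80 |

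The p-value is identical for nearly full agreement and nearly full disagreement. The sign of rho does separate them in a 2×2 table.

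**2. Fisher-type exact test, three classes, 21 specimens, every case given the wrong class**

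Table [[0,7,0],[0,0,7],[7,0,0]]: agreement is 0/21, kappa is (0 − 1/3)/(2/3) = −0.50, and the exact p is 6 × (7!)⁶ / (21! × (7!)³) = 1.5 × 10⁻⁸. The association is highly significant with no agreement at all.

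**3. The reverse case, and a caution about kappa**

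Table [[18,1],[1,0]]: agreement is 18/20 = 90%, but Fisher p = 1.0. Expected agreement is (19×19 + 1×1)/400 = 0.905, so kappa is (0.900 − 0.905)/0.095 = −0.05. With skewed margins kappa alone misleads, so percent agreement has to come first.

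**4. Spearman's rho, three unordered classes, 18 specimens**

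Table [[5,1,0],[0,5,1],[0,0,6]]: agreement is 16/18 = 89%. Expected agreement is (6×5 + 6×6 + 6×7)/18² = 108/324 = 1/3, so kappa is (0.889 − 0.333)/0.667 = 0.83. Renumbering the classes identically for both readings gives:

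| Class placed in the middle | Spearman rho |
|---|---|
| second | 0.93 |
| first | 0.80 |
| third | 0.78 |

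Agreement and kappa do not change. With a less concordant table, [[6,1,0],[3,4,0],[0,2,5]] (15/21 = 71% agreement, kappa 0.57), rho is 0.80, 0.53 or 0.40 under the same three numberings.

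**5. Precision of percent agreement**

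Clopper-Pearson 95% intervals at an assumed 70% agreement, for assumed numbers operated on:

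| Operated | Agreeing | Exact 95% CI |
|---|---|---|
| 10 | 7 | 35% to 93% |
| 20 | 14 | 46% to 88% |
| 30 | 21 | 51% to 85% |
| 60 | 42 | 57% to 81% |

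**The case against.** The strongest reply is that the sentence may not be the concordance analysis at all. It speaks of qualitative findings and histopathological abnormalities, and mentions neither concordance nor diagnosis. The Intervention and evaluation protocol section lists many single signs, such as cortical thickening, transmantle sign and intracortical black line, along with lesion size and number. Relating such features to histology is a sensible aim, association tests suit it, and three methods might be offered so that each type of variable gets a fitting one. The agreement measure for the diagnosis could then sit in the full protocol or analysis plan, which is not shown.

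This reading is possible, and it is why the point is conditional. It does not remove the point. No other sentence in the section covers the concordance outcome, the wording does not confine itself to individual signs, and the method is tied to distribution and not to scale. Someone following the text would apply association tests to the outcome.

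Three stronger readings are tempting and should not be drawn:

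- A reader might infer that none of the named methods suits nominal diagnoses. Fisher's test does; its limit is that it does not measure agreement.
- A reader might infer that the analysis can never tell agreement from disagreement. In a 2×2 table the sign of rho does so, and a Fisher p-value printed beside its table would show the direction.
- A reader might infer that the outcome would be uninterpretable. The documents do not say that the cross-table will be withheld, and systematic opposition between UHF MRI and histology is an extreme construction.

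**Conclusion.** The point holds in a limited form. The plan names a concordance outcome and supplies only association methods for MRI against histopathology. Applied to that outcome, they give a p-value that can be the same at 90% and 10% agreement, or, with three or more unordered classes, a coefficient that moves with the numbering (0.78 to 0.93 in one table, 0.40 to 0.80 in another).

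The conclusion rests on two assumptions: that the sentence is meant to serve the concordance outcome, which is inferred because nothing else does, and that the diagnosis classes are unordered, since the article gives no order. The tables show how the methods behave and do not predict the trial's data. Both primary outcomes, planned as point estimates with 95% confidence intervals, are untouched. This is a worthwhile correction to a secondary outcome.

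**What to change.** In the Statistical analysis section, state that concordance will be assessed in resected patients only, as the proportion whose consensus UHF diagnosis class equals the histopathology class. Report it with an exact 95% CI and the full cross-table, and give unweighted Cohen's kappa as a supplement. Fix the list of diagnosis classes before analysis. Keep the association methods for individual MRI features against histology, and choose among them by measurement scale.

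This takes a sentence or two and uses the same data. The drawback is that the interval may be wide if few patients are operated on. That uncertainty exists whichever method is used; the interval shows it openly.
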